### Inclusion and exclusion criteria

#### Inclusion criteria

Pregnant women were eligible for the study if they had at least one of the following risk factors: BMI ≥ 25 kg/m^2^, GDM or any signs of glucose intolerance or macrosomic newborn (≥ 4500 g) in any earlier pregnancy, type 1 or 2 diabetes in first or second grade relatives or age ≥ 40 years.

#### Exclusion criteria

Women were excluded if they had at least one of the following: a pathological value in the baseline oral glucose tolerance test (OGTT) at 8-12 weeks' gestation (blood glucose > 5.3 mmol/l at fasting, > 10.0 mmol/l at 1-hour or >8.6 mmol/l at 2-hour), pre-pregnant type 1 or 2 diabetes, inability to speak Finnish, age < 18 years, twin pregnancy, physical restriction preventing from physical activity, substance abuse, treatment or clinical history of psychiatric illness.

### Intervention

The trial will continue from the first maternity clinic visit (at 8-12 weeks' gestation) until 37 weeks' gestation (Figure 2). The recommendations for gestational weight gain are discussed and the primary physical activity counseling takes place at the first visit. The primary dietary counseling session is implemented during the visit at 16-18 weeks' gestation. Both physical activity and dietary counseling are boostered at subsequent visits; physical activity at four and diet at three visits (Figure 2).

**Figure 2 F2:**
[figure not shown]
**Timing of the counseling in the trial clinics**.

Both physical activity and dietary counseling are based on the model of Laitakari and Asikainen [33] which incorporates two central behavioral models, PRECEDE-PROCEED [34] and Stages of Change ([35]. The model has been found applicable in occupational health care [36] and in the pilot study on preventing excessive gestational weight gain [27,28]. The allocated time regarding both physical activity and dietary counseling was 20-30 minutes for primary counseling sessions and 10-15 minutes for each of the booster sessions [27].

#### Counseling on gestational weight gain

The recommendations for total gestational weight gain were 12.0-18.0 kg for women with pre-pregnancy BMI 18.5-19.9 kg/m^2^, 11.5-16.0 kg for women with BMI 20.0-26.0 kg/m^2 ^and 7.0-11.5 kg for women with BMI ≥ 26.0 kg/m^2 ^[37]. These recommendations were introduced at the first maternity clinic visit. In order to help the participant to reach her BMI-specific recommendation, her rate of weight gain was monitored until the end of pregnancy by using a BMI-specific weight gain chart [38]. This chart was included in the participant's own follow-up notebook. Allocated time for discussion on the weight gain recommendations and weight monitoring was 5 minutes at each of the five visits.

#### Physical activity counseling

According to current American [39,40] and Canadian guidelines [41] the general physical activity recommendation for health [42] applies to pregnant women without medical or obstetric complications. This has been restated in the most recent physical activity recommendation updated by the Physical Activity Guidelines Advisory Committee [43]. The general recommendation for fitness [44] is also valid during pregnancy among women, who have been regular exercisers before pregnancy and who have uncomplicated pregnancy [40]. Borg's [45,46] visual scale of perceived exertion (RPE) including ratings 6-20 is suggested for intensity assessment. The objectives of the physical activity counseling were:

1) To increase leisure time physical activity (LTPA) of those pregnant women, who are not fulfilling the recommendations, to the recommended level for health.

2) To maintain LTPA of those pregnant women, who are already fulfilling the recommendation for health.

3) To maintain or adjust LTPA of those pregnant women, who are already fulfilling the recommendation for fitness.

The structure and the topics of the physical activity counseling sessions were guided by the counseling card, which was filled in for each participant at each session. At the primary session, the participant's current leisure-time physical activity (LTPA) and her need and opportunities for LTPA were assessed and the benefits and limitations on LTPA were discussed with the help of a take-home leaflet. The nurse and participant agreed on a weekly action plan including LTPA modes and their frequency, duration and intensity, which was based on RPE ratings 6-20 [45,46].

The minimum weekly LTPA dose entered progressively in the action plan was 800 MET (multiples of resting metabolic equivalents) minutes. Thus is in line with Haskell et al [47] suggesting the minimum of 450 to 750 weekly MET minutes for health. Nurses calculated MET minutes from the action plans by multiplying the weekly minutes and the MET value of each LTPA mode and by summing up the numbers. Also light-intensity LTPA (MET value 3) was included to the plan due to participants' different LTPA backgrounds. RPE 6-11 equaled three METs, 12-14 five METs and 14-20 seven METs [41,44,48,49]. Compliance with the action plan was monitored at the booster sessions with a LTPA log, which was part of the participant's follow-up notebook. If the action plan was revised, also the weekly MET minutes were recalculated.

#### Monthly thematic meetings on physical activity

During the primary physical activity counseling visit the participants were offered an opportunity to participate monthly thematic meetings on physical activity including group exercise. The sessions were arranged after the working hours close to the maternity clinics and the women's living area. The purpose of the meetings was to support physical activity counseling by providing the participants social support for behaviour change and by introducing them various ways of being physically active. Sessions consisted of five different themes on a non-stop basis, which were:

Theme 1. Physical activity is worthwhile during pregnancy: the benefits of physical activity, current physical activity recommendations during pregnancy.

Theme 2. Walking is pleasant and effective: putting technique and footwear in order.

Theme 3: More alteration and goals for walking: using pedometers and poles.

Theme 4: Preventing urinary incontinence: pelvic muscles and training.

Theme 5: Integrating physical activity to family life: physical activity after pregnancy.

The dates of all the sessions were informed during the primary counseling visit. The participants were to attend to the next meeting after their recruitment but were eventually able attend to every one of them during the pregnancy. The duration of each session was two hours: 30 minutes for getting acquainted, 30 minutes for the theoretical basis related to the theme and 1 hour for the group exercise related to the theme. In all the sessions RPE was used in assessing the intensity of exercise.

The sessions were instructed by the physiotherapists of local health care centres or private clinics. A week before each meeting a reminder of the forthcoming meeting was transmitted via short message service from the research institute to each participant. A week after the meeting the instructor contacted all the participants by telephone to encourage them to continue with their weekly action plans and to get feedback on the meeting from those who had attended. The instructors were trained and provided with all the material needed for the theoretical and practical parts of the thematic meetings. Also, they were paid for the time needed for the training, for the actual meetings and for making the telephone calls.

#### Dietary counseling

The aim of the dietary counseling was to help the participants to achieve a diet containing saturated fat ≤ 10%, polyunsaturated fat 5-10% and total fat 25-30% (includes saturated, monounsaturated, polyunsaturated and trans fatty acids) of total energy intake and fiber 25 to 35 g/day. This aim was selected based on the Finnish dietary recommendations[50], studies on the association of diet and development of GDM [15-17] study that was successful in preventing type 2 diabetes mellitus in Finland [51]. To achieve this, the dietary counseling focused on the objectives were:

1) To use vegetables, fruit and berries preferably at least 5 portions (400 g) a day.

2) To select mostly high fiber bread (≥ 6 g fiber/100 g) and other whole-meal products.

3) To select mostly fat-free or low-fat versions of milk and milk products (e.g. yoghurt, cheese, ice cream) and of meat and meat products.

4) To eat fish at least twice per week (excluding the fish species not recommended for pregnant women).

5) To use moderate amounts of soft table spreads on bread, oil-based salad dressing in salad and oil in cooking and baking.

6) To use seldom and only in small portion sizes foods high in fat.

7) To use seldom and only in small portion sizes snacks containing lots of sugar and/or fat (e.g. sweets, high-sugar drinks, cookies, ice cream, sweet and salty.

The nurse used a counseling card reminding her about the counseling topics and to which she was able to make remarks at each counseling session. At the primary counseling session, the nurse assessed the participant's current diet by using a check list containing the above mentioned objectives. The nurse asked the participant whether each of the objectives was fulfilled in her current diet either mostly, partly or not at all. The dietary recommendations were highlighted to the participants with the help of a leaflet on diet during pregnancy (Raskausajan liikunta ja ravitsemus, MLL & Sydänliitto), which was also given to the participant. Discussion included participant's needs for dietary changes, as well as her opportunities for and barriers to making the changes. The nurse encouraged the participant to maintain those objectives that were already fulfilled. Of the objectives that were not fulfilled, the participant selected 2-3 objectives which she wanted to improve in her diet. As a consequence of this discussion, individual objectives were set for the next visit (e.g. "to increase the intake of vegetables, fruit and berries from 2 to 4 portions/day" or "to decrease the intake of high-sugar snacks from 3 to 1 portion/day"). These objectives were written down in the follow-up note book. The participant was asked to keep weekly record whether she achieved her objectives or not. At each booster visit, the follow-up notebook was checked, the records were discussed and the objectives were revised if needed (e.g. set at higher level or changed to other objectives). The nurses also discussed about other dietary issues important for the participants (e.g. the special dietary restrictions during pregnancy).

#### Control group

The women in the control maternity clinics received routine care and no extra counseling beyond usual practices or group exercise were arranged. However, the routine maternity care includes some dietary and physical activity counseling as shown in our pilot study [27,28].

#### Non-participants

Women who were not willing to participate in the RCT were asked to complete the baseline questionnaire and to give their consent for linking their information to medical birth registry.

### Outcome measurements

Outcome measurements are assessed at six times during pregnancy (8-12, 16-18, 22-24, 26-28, 32-34, 37-39 week's gestation) and twice postpartum (6 weeks and 1 year) (Figure 3, Table 1).

**Table 1 T1:** Timing of questionnaires, maternal physical measurements and laboratory tests.

	Weeks' gestation						Postpartum follow-up	
	8-12	16-18	22-24	26-28	32-34	36-37	6 weeks	1 year
Questionnaires								
Background questions	X							
Physical activity	X			X		X		X
Food frequency	X			X		X		X
15 D quality of life	X			X		X	X	X
Adverse events		X	X	X	X	X		
Use of insulin therapy						X		X
Workability				X		X		X
Return to work								X
Physical measurements								
Height	X							
Weight	X	X	X	X	X	X	X	X
Blood pressure	X	X	X	X	X	X	X	X
Waist circumference								X
Laboratory tests								
Oral glucose tolerance test	X			X				X
Blood samples	X			X				X

**Figure 3 F3:**
[figure not shown]
**Design and timetable of the study: cluster-randomized controlled trial (RCT), 1-year follow-up and linkage to the medical birth registry**.

*The primary maternal outcome *of the trial is the proportion of women diagnosed with GDM, as assessed by oral glucose tolerance test during 26-28 week's gestation and the weight of the newborn adjusted for gestational age.

*Secondary outcomes *of the trial are gestational weight gain and need of insulin treatment during pregnancy determined at time of possible GDM diagnosis (earliest 26-28th week of pregnancy based on OGTT). Additional outcomes are changes in maternal physical activity (frequency and duration of total and domain-specific leisure time physical activity) and dietary habits (food choices related to the objectives of counselling, fibre intake (g/day) and proportions of saturated, polyunsaturated and total fat of total energy intake), maternal quality of life (profile of 15 health-related dimensions during pregnancy). Direct and indirect costs during pregnancy and the cost-effectiveness of the trial (based on QALYs) are calculated. Changes related to blood lipids (cholesterol, HDL-cholesterol, triglycerides, LDL-cholesterol, oxidized lipoproteins) and other biological markers of fat metabolics (IGF, IGFBp-3, C-peptide, leptin, adiponectin, para-oxonase) are determined both during pregnancy and one-year postpartum.

*The outcomes of the 1-year follow-up study *are maintenance of possible changes in physical activity and dietary habits, incidence of metabolic syndrome based on the International Diabetes Federation criteria [52], perceived workability, quality of life (RAND-36 scale), depression (Beck scale) and proportion of women returning to work after maternity leave.

*Medical birth registry linkage *includes information on perinatal outcomes (complications during pregnancy or delivery, such as pre-eclampsia, cesarean section rate and need for labour induction) and incidence of GDM among non-participants.

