Lifestyle modifications have been shown valuable adjunctive therapy in the treatment of GDM [23]. Moreover, there is encouraging evidence on the impact of lifestyle interventions to prevent the progression of GDM to type 2 diabetes in women with history of GDM [24]. The small trials by Mottola et al. [25] and Hui et al [26] showed promising results in preventing GDM with nutrition and physical activity modification. In our own pilot study (n = 105), pregnant women who had intensified dietary and physical activity counseling at routine maternity clinic visits were able to change their diet to favourable direction and to maintain at least moderate physical activity more often than the women with routine counseling [27,28]. Interestingly, there were no high birth weight newborns in the intervention group, but eight of them (15%) in the control group, suggesting that the intervention may have had beneficial effect on maternal glucose tolerance.

The evidence for the effect of lifestyle modification in preventing GDM will accumulate in the future from ongoing studies by Chasan-Taber et al [29] and Oostdam et al [30] and from our study presented here. The *primary objective *of our trial is to show whether individual counseling on physical activity, diet and gestational weight gain can have preventive effect on the development of GDM. *Secondary objectives of our trial *are to evaluate maternal and child weight development, maternal metabolic changes, and changes in maternal physical activity and dietary habits and quality of life. Cost-effectiveness of the trial is evaluated since the prevention of GDM is important in order to reduce direct health care costs, such as hospital days and surgical procedures and indirect costs due to sick leave during pregnancy. To date no cost-effectiveness studies have been published on the prevention of GDM. The purpose of this paper is to describe the design and the methods of a cluster-randomized controlled trial (RCT) to prevent GDM and its 1-year follow-up.

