### Power calculations and sample size

The randomization of maternity clinics as clusters instead of women as individuals was taken into account in the power calculations [66]. When planning the RCT, no published studies on prevention of GDM among women at risk or data on decrease in the incidence of GDM were available. The power calculations for pair-matched study were based on the assumption of detecting a 40% reduction of incidence of GDM from 40% in the control clinics to 24% in the trial clinics. The power of the study was 0.80, significance level 0.05 and coefficient of variation of rate between clusters, indicating cluster sampling, 0.1. The dropout rate during the study (estimated 25%) was taken into account in the sample size calculations. Thus, a total number of 560 women should be recruited to the study. The number of women in the end of the study would thus be 210 + 210 (7+7 clinics, 30 women/clinic).

Success in recruitment and proportion of drop-outs (25%) were estimated based on the pilot study [28,67]. Our recruitment target seemed feasible since the annual number of deliveries in Pirkanmaa region was approximately 5000 [31] and at least fourth of these women were estimated to fulfill the inclusion criteria of this study.

The sample available for the 1-year follow-up (n = 462) is adequate to discover 5-20% difference of metabolic syndrome in trial and control groups. Intracluster correlation coefficient in the current study is estimated as 0.12 (valid when 0.10-0.30) [68].

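### Newborn weight is declared primary alongside GDM, but the primary objective, the 0.05 level, the 0.80 power and the sample of 560 concern GDM alone

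*Protocol article*

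**What the plan says.** All references are to the protocol article.

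- **Outcome measurements.** The primary maternal outcome, in the singular, "of the trial is the proportion of women diagnosed with GDM, as assessed by oral glucose tolerance test during 26-28 week's gestation". The sentence then continues with "and the weight of the newborn adjusted for gestational age". The secondary outcomes listed next are gestational weight gain and need for insulin; newborn weight is not among them.
- **Background, objectives.** The primary objective "is to show whether individual counseling on physical activity, diet and gestational weight gain can have preventive effect on the development of GDM". No other primary objective is given. The secondary objectives "are to evaluate maternal and child weight development, maternal metabolic changes", among other things.
- **Power calculations and sample size.** The trial is sized for "detecting a 40% reduction of incidence of GDM from 40% in the control clinics to 24% in the trial clinics". One level and one power are given: "The power of the study was 0.80, significance level 0.05". No effect size or standard deviation for newborn weight appears.
- **Statistical analysis.** Multilevel analysis is the main method. The section does not say how the two outcomes named as primary relate to each other.

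**The concern.** The two endpoints are different in kind. One is binary, maternal and measured in mid-pregnancy; the other is continuous, neonatal and measured at delivery. They are not components of a composite, so the sentence declares two primary results, while the objective and the design figures recognise one.

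What is at stake is the meaning of a split result. Suppose GDM is null and newborn weight is significant. The outcome sentence would allow this to be called a positive primary result; the primary objective would not. The case is foreseeable. The Background reports that in the pilot no newborn in the intervention group had a high birth weight, against eight (15%) in the control group. The power section says that no data on a decrease in GDM incidence were available at planning. Newborn weight is thus the endpoint with a favourable prior signal, and GDM is the one for which the trial was sized.

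**Working it through.** **Step 1. Does the stated sample size involve newborn weight?**

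Inputs from Power calculations and sample size: control rate p0 = 0.40, trial rate p1 = 0.24, n = 30 women per cluster at the end of the study, 7 + 7 clusters in a pair-matched design, power 0.80, level 0.05, 25% dropout, and k = 0.1 from "coefficient of variation of rate between clusters, indicating cluster sampling, 0.1". The sidedness of the test is not stated; two-sided is assumed.

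Number of pairs for a matched design:

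c = 2 + (z_alpha + z_power)² × [p0(1−p0)/n + p1(1−p1)/n + k²(p0² + p1²)] / (p0−p1)²

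- Bracket: 0.24/30 + 0.1824/30 + 0.01 × (0.16 + 0.0576) = 0.008000 + 0.006080 + 0.002176 = 0.016256
- Divided by 0.16² = 0.0256: 0.635
- (1.960 + 0.842)² = 7.849
- c = 2 + 7.849 × 0.635 = 6.98, so 7 pairs
- 7 × 2 × 30 = 420 women at the end; 420 / 0.75 = 560 recruited

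This reproduces the plan's 7 + 7 clusters, 210 + 210 women and 560 recruited. A one-sided test would give 5.93, so 6 pairs, which supports the two-sided reading. Newborn weight plays no part in the figure.

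**Step 2. Error rate if success on either outcome counted, each tested at two-sided 0.05**

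- Independent tests: 1 − 0.95² = 0.0975, which is 1.95 times 0.05
- Correlated test statistics (bivariate normal; the correlations are assumptions, as the article gives none):

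| Correlation | Chance of at least one false positive |
|---|---|
| 0 | 0.0975 |
| 0.3 | 0.0951 |
| 0.5 | 0.0907 |
| 0.7 | 0.0835 |

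**Step 3. If both outcomes had to succeed**

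The type I error of the joint claim would not exceed 0.05. Joint power could not exceed the power for GDM, about 0.80, and would be lower unless newborn weight were almost certain to succeed whenever GDM did. It cannot be calculated, because no effect size or standard deviation for newborn weight is given.

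**Step 4. If alpha were split, 0.025 for each outcome**

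Power for GDM with 7 pairs of 30 is Φ(√[(7−2) × 0.0256 / 0.016256] − z_alpha), and the square root is 2.806.

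- At 0.05: Φ(2.806 − 1.960) = 0.801
- At 0.025: Φ(2.806 − 2.241) = 0.714

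Restoring 0.80 at the 0.025 level needs c = 8.04, so 9 pairs of 30 (540 completing, 540 / 0.75 = 720 recruited), or 7 pairs of 38 (532 completing, 710 recruited).

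**Step 5. If GDM is tested first and newborn weight only after a significant GDM result**

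If GDM is truly null, any false claim must first pass the GDM test at 0.05. If GDM is truly affected and newborn weight is not, the only possible false claim is newborn weight, again at 0.05. The family-wise error is at most 0.05, GDM keeps its 0.05 level, and step 1 still gives 560.

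**The case against.** The strongest reply is that this is a condensed journal article and no statistical analysis plan is shown. Testing order and alpha allocation commonly belong there, so their absence is no fault. That stands, and the point does not rest on it. It rests on two statements within the article that disagree about what is primary. An analysis plan could add a rule, but it could not make the objective, the outcome sentence and the sizing agree.

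A reader might infer that the trial runs at nearly twice its stated error rate. The article does not support this. It nowhere says that success on either outcome is enough, and 9.75% also needs independent tests. Independence is doubtful, since the Background links GDM to macrosomic newborns.

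A reader might also infer that the Background expressly makes newborn weight secondary. That is too strong. Child weight development may mean growth after birth, and the Background uses similar wording for children's weight apart from its remark on macrosomia. The overlap is supporting evidence only; the mismatch with the sole primary objective holds without it.

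It can further be said that the abstract's aim, the objective, the power calculation and the discussion all point to GDM, and that the outcome sentence speaks of a maternal outcome, so newborn weight may be meant as the lead neonatal outcome. This is a fair guess at intent and favours the repair below. The sentence itself does not say so.

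Finally, the GDM test at 0.05 is sound whatever newborn weight is called. That is true and limits the damage to claims that rest on newborn weight.

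**Conclusion.** The point holds as an inconsistency about what is primary. Two distinct endpoints are declared primary, while the objective, the significance level, the power and the sample size belong to one of them. The stated 0.05 and 0.80 are correct for GDM and do not describe the primary claim as declared.

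The size is conditional. Under an either-outcome rule the false-positive rate is at most 9.75%, and about 8.35% to 9.51% at assumed correlations of 0.7 to 0.3. Under a both-outcomes rule there is no inflation, but joint power is unknown. Under an equal split GDM power is about 0.71. All the power figures assume a two-sided test and the article's own cluster inputs.

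**What to change.** Issue a dated clarification before the outcome analysis that:

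- names GDM by OGTT at 26-28 weeks as the single primary outcome, tested at two-sided 0.05;
- names newborn weight adjusted for gestational age as the first key secondary outcome, tested at 0.05 only if GDM is significant;
- brings the objectives in the Background, the Outcome measurements section and the Power calculations section into line with this.

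No recruitment or data collection changes, and the sample stays at 560.

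There are two costs. Newborn weight cannot support a confirmatory claim if GDM is null. And since the article describes recruitment in the past tense and already states a follow-up sample of 462, this changes the status of a declared primary outcome in a trial that has been carried out; it must be justified and disclosed as such. A both-outcomes rule or an alpha split would also remove the ambiguity, but the first leaves power unknown and the second gives up about 9 percentage points of GDM power (0.801 − 0.714) unless more women are recruited.

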**Discussion:**

The study will provide information on the effectiveness and cost-effectiveness of gestational physical activity and dietary counseling on prevention of GDM in a risk group of women. Also information on the prevalence of GDM and postpartum metabolic syndrome will be gained. Results on maintaining the possible health behaviour changes are important in order to prevent chronic diseases such as cardiovascular disease and diabetes.

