#### Physical measurements

Maternal anthropometric measures. Information on maternal anthropometric measurements were obtained from the standard maternity card. Pre-pregnancy weight was self-reported.The nurses measured body weight of the women at each study visit during pregnancy and height at the first visit. Total gestational weight gain was calculated based on the pre-pregnancy weight and last measured weight during pregnancy. One year postpartum the women were invited to local maternity clinics or to the UKK institute for weight, waist circumference and blood pressure measurements in order to determine the incidence of metabolic syndrome.

Foetal anthropometric measures. Weight of the newborn and gestational age was obtained from medical records of the delivery hospital or from the maternity card. Details related to delivery and perinatal complications will be received from medical birth registry.

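### The 1-year metabolic syndrome outcome is called incidence, but the measurements described give prevalence: there is no baseline waist, no baseline classification and no exclusion of existing cases

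*Protocol article*

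**What the plan says.** The Outcome measurements section of the protocol article names, among the outcomes of the 1-year follow-up, the "incidence of metabolic syndrome based on the International Diabetes Federation criteria". The Physical measurements section repeats the term: women were invited back at one year "for weight, waist circumference and blood pressure measurements in order to determine the incidence of metabolic syndrome".

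In Table 1 the row "Waist circumference" has one mark, in the 1-year column. Weight and blood pressure are marked at every visit. The oral glucose tolerance test (OGTT) and blood samples are marked at 8-12 weeks, 26-28 weeks and 1 year.

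The metabolic exclusions at entry are a pathological OGTT at 8-12 weeks and diabetes before pregnancy ("pre-pregnant type 1 or 2 diabetes, inability to speak Finnish, age < 18 years, twin pregnancy" is the relevant part of the list). Metabolic syndrome, raised blood pressure and abnormal lipids are not listed. Entry is through risk factors: "Pregnant women were eligible for the study if they had at least one of the following risk factors: BMI ≥ 25 kg/m^2", or earlier glucose intolerance, an earlier macrosomic newborn, a family history of diabetes, or age 40 or over.

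Two other places describe the outcome differently. The Discussion paragraph of the abstract says that "information on the prevalence of GDM and postpartum metabolic syndrome will be gained". The sample-size section says "The sample available for the 1-year follow-up (n = 462) is adequate to discover 5-20% difference of metabolic syndrome in trial and control groups", with no mention of new cases or of women free of the syndrome at baseline.

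**The concern.** Incidence counts new cases among people who did not have the condition at the start. That requires either a baseline classification or an entry rule that removes existing cases. The article describes neither for metabolic syndrome, in women chosen partly because they are overweight. If the 1-year proportion is reported under the name incidence, it will be read as a rate of new-onset disease, and a difference between arms as prevention of new onset. The article's main Discussion section names prevention of chronic disease as a possible long-term benefit, so that reading comes easily. The data as described cannot support it.

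**Working it through.** The article states no figure for this outcome that could be reproduced. The point is settled by setting its sections side by side.

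**Step 1: what incidence would need.** The trial's own primary outcome is a useful contrast. For gestational diabetes there is an OGTT at 8-12 weeks, women with a pathological value are excluded, and the test is repeated at 26-28 weeks. A positive result at the second test is then reasonably called new.

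**Step 2: what exists for metabolic syndrome.**

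| Requirement | Gestational diabetes | Metabolic syndrome at 1 year |
|---|---|---|
| Defining measurement at baseline | OGTT at 8-12 weeks | No waist at any visit before 1 year (Table 1) |
| Existing cases removed at entry | Yes, pathological OGTT | No; only pathological OGTT and diabetes (Exclusion criteria) |
| Baseline status classified | Yes, by the exclusion | Not stated anywhere |
| Analysis limited to women free of it | Follows from the exclusion | Not stated; the sample-size section refers to the whole follow-up sample |

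**Step 3: consequence.** A woman with the syndrome before pregnancy who still has it at 1 year counts the same as a woman who developed it in between. The quantity obtained is the proportion affected at 1 year, which is prevalence, the word used in the abstract.

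**Step 4: direction of the effect on the comparison.** Let b be the share of women in each arm with pre-existing, persisting disease, and i the proportion of the others who develop it. Then:

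1-year proportion = b + (1 - b) × i

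The documents give neither b nor i. Assume i = 20% in control and 10% in the trial arm, with b equal in both arms:

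| b (assumed) | Control | Trial | Ratio | Difference |
|---|---|---|---|---|
| 0% | 20.0% | 10.0% | 0.50 | 10.0 points |
| 5% | 0.05 + 0.95 × 0.20 = 24.0% | 0.05 + 0.95 × 0.10 = 14.5% | 0.60 | 9.5 points |
| 10% | 0.10 + 0.90 × 0.20 = 28.0% | 0.10 + 0.90 × 0.10 = 19.0% | 0.68 | 9.0 points |
| 15% | 0.15 + 0.85 × 0.20 = 32.0% | 0.15 + 0.85 × 0.10 = 23.5% | 0.73 | 8.5 points |

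Both proportions rise and the ratio moves towards 1, while the absolute difference shrinks only by the factor (1 - b). The table shows direction. It is not an estimate for this trial.

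**The case against.** The strongest reply is that this is loose wording. The article uses prevalence and incidence interchangeably for gestational diabetes too, the sample-size section speaks only of a difference between groups, and the stated objectives do not promise an effect on new-onset metabolic syndrome. That is fair as an account of how the word got there. It does not remove the inconsistency: two sections define the outcome as incidence, and one of them gives incidence as the purpose of the measurement.

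A second reply is that a baseline status could be approximated. Height, weight, blood pressure, OGTT and lipids are recorded at 8-12 weeks, and pre-pregnancy weight is self-reported. This stands in part, so it would be too strong to say that nothing about baseline status can be recovered. But the proxy would lack waist, would rest largely on values taken in pregnancy, and is not described. The OGTT and diabetes exclusions remove some existing cases through glucose, but not those arising from the other components.

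Three stronger readings are tempting, and the documents do not support them:

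- **That the comparison between arms is biased.** It is not. Municipalities were randomised, and comparing 1-year proportions is valid whatever the outcome is called. Chance imbalance between 14 clusters can affect any outcome. The label does not cause it, and pair-matching and the multilevel model address it in part.
- **That a particular share of the reported cases must be pre-existing.** The documents give no rate at baseline or at 1 year. Any such share also assumes that every baseline case persists, although counselling on diet and activity might reverse some.
- **That women pregnant again at the 1-year visit should be left out.** No section bears on this. Removing women for an event after randomisation would sit badly with the intention-to-treat principle in the Statistical analysis section.

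**Conclusion.** The point holds as a mismatch between the name of a follow-up outcome and what is measured. The article contradicts itself: incidence in the Outcome measurements and Physical measurements sections, prevalence in the abstract. Only prevalence fits the measurements and entry rules described.

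The consequence is limited. The primary outcome, the randomisation and the primary sample size are untouched, and the arm comparison of 1-year proportions stands. What is lost is the right to describe a difference as prevention of new-onset metabolic syndrome. Pre-existing cases would tend to pull a ratio towards 1, provided they are about equally common in both arms and mostly persist. The documents do not allow the amount to be estimated.

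The conclusion rests on the article as shown. If the full protocol or analysis plan contains a baseline classification, the article's wording should say so.

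**What to change.** In the Outcome measurements and Physical measurements sections, name the outcome *prevalence (proportion) of metabolic syndrome at 1 year postpartum*, in line with the abstract. State that no conclusion about new-onset disease will be drawn from it.

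Within the multilevel model already planned, adjust the arm comparison for pre-pregnancy BMI and for blood pressure, fasting glucose and lipids at 8-12 weeks. All of these are already collected. The aim is better precision and some protection against chance imbalance; adjustment does not turn prevalence into incidence. Two cautions should be written beside it: the 8-12 week values are taken in early pregnancy, so they are imperfect markers of the state before pregnancy, and with only 14 clusters the covariate set should be kept small and fixed in advance.

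The cost is a change of wording, slightly more analysis and a weaker claim than incidence would carry. No new data are needed.
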